### Study interventions

#### Intervention group (ISDM programme)

The intervention (Table 1) comprises a decision aid booklet [17] and a corresponding counselling module. The counselling is provided by diabetes educators of the participating clinic. Patients are guided through the decision making process, by 1) jointly assessing the patient’s individual heart attack risk, 2) providing outcome probabilities of the available preventative treatment options, and 3) supporting to set individual goals regarding smoking cessation, glucose control, blood pressure control, and statin treatment. A physician is to be consulted if patients wish a change of treatment regimens.

**Table 1 T1:** Characteristics of intervention and control intervention

	**ISDM programme**	**Control-intervention**
**Components**	Decision aid booklet “On the prevention of heart attack in type 2 diabetes” [17]	Brochure “Stress” [27]
	Curriculum	Curriculum
	Media: Specific wall charts, worksheets, question cards, and a magnet board	Media: Specific wall charts, worksheets, and a relaxation exercise
**Duration**	60-90 minutes	60-90 minutes
**Group size**	4 participants	4 participants

The counselling module takes about 90 minutes. Patients are asked to read and work through the DA, at least one week before the group counselling session.

For study purposes, two diabetes educators have attended the ISDM programme specific train-the-trainer module given by a research fellow of the Unit of Health Sciences and Education of the University of Hamburg. In order to ensure educational fidelity, certified diabetes educators provide the counselling sessions. To ensure fidelity of the evidence-based contents, the sessions are videotaped and analysed. If required, the research fellow gives feedback for optimisation.

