### Outcomes

Primary outcome measure (Table 2) is the level of patient knowledge relating to the concept of risk, the notion of heart attack risk, and the benefits and harms of preventative treatment. Knowledge is captured by a standardised questionnaire consisting of 12 questions to assess *comprehension of risk information* and *realistic expectations*[28], plus one question to assess *numeracy*[29].

**Table 2 T2:** Data collection

**Outcomes**	**Measures**	**No. of items**	**Follow-up**^ ***** ^
Knowledge	• Questionnaire developed on the basis of Bloom’s taxonomy [30] and evidence-based information on heart attack prevention in type 2 diabetes [17] (updated 08/2012)	13	T1, T2
Realistic expectations	• Questionnaire developed on the basis of ISDM-counselling	6^**^	T1, T2
Numeracy	• Numeracy test (one minute test for general population) [29]	1^***^	T1
Treatment goals	• Statin medication, levels of blood pressure and glucose control, smoking, and patient’s prioritized treatment goal are documented on a standardised form	1 for each goal	T1
Achievement of treatment goals	• Statin medication (patient medication boxes)	1	T2
	• Blood pressure (self-monitoring, standardised measure if not available)	1	T2
	• HbA1c-level (standardised measure)	1	T2
	• Smoking cessation (question by diabetes educator)	1	T2
Medication	• Variation in medication intake (statins, antihypertensive drugs, glucose-lowering agents) are documented using medical records (T1) and by verifying patients’ pill-packages (T2).	3	T1, T2

^*^ T1; at the end of the counselling session; T2; at 6 months follow-up.

^**^ 6 out of 13 questions of the knowledge test.

^***^ 1 out of 13 questions of the knowledge test.

Secondary outcome measures comprise 1) sustainability of knowledge; 2) achievement of individual treatment goals regarding the use of statins, levels of blood pressure and glucose control, and smoking; 3) achievement of treatment goals prioritised by the individual patients; 4) medication uptake from T1 to T2.

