### Data collection

The EPRS of the clinic and standardised forms are used to collect baseline characteristics and outcome measures.

Baseline characteristics include age, gender, first-language, social status [31], smoking status, blood pressure, LDL-cholesterol, total cholesterol, HbA1c, current medication, and previous participation in diabetes patient education programmes.

Baseline risks of myocardial infarction are calculated by using a risk assessment tool based on age, smoking status, and clinical parameters. The tool is derived from the Framingham function and calibrated [32] to the average heart attack risk in the German population.

Knowledge is assessed directly after the counselling session and at 6 months follow-up. The individual treatment goals regarding smoking cessation, glucose control, blood pressure control, and statin treatment are assessed after the counselling session. Achievement of treatment goals is assessed during a consultation at 6 months follow-up. Current medication is monitored by verifying patients’ pill-packages. Smoking status is assessed by using a standardised interview question. Current blood pressure values (mean of 2 weeks) are extracted from patient diaries. If values are not available, blood pressure is measured before counselling by a nurse applying a standardised procedure (after 5 minutes seated position). Glucose control is assessed by measuring HbA1c-levels [33].

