#### Secondary outcomes

Unpaired t-tests will be used to compare mean knowledge scores at follow-up. Fisher’s exact test will be used to compare proportions of sufficient knowledge after counselling and at follow-up. Participants will be rated as having sufficient knowledge if they correctly answered at least 8 out of 12 questions. Unpaired t-tests will be used to compare average individual differences between planned and achieved values of blood pressure and HbA1c. Fisher’s exact tests will be used to compare the groups regarding rates of individual goal achievement (yes/no): statin choice, smoking status, blood-pressure (defined as reaching 80% to 120% of the goal), and HbA1c (defined as reaching 80% to 120% of the goal). Mann Whitney U-Test will be used to compare the medication uptake from T1 to T2 (increase/unchanged/decrease).

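### Medication change is counted from the end of counselling, so a programme-prompted change already in the record by then can be coded as unchanged; count it from baseline

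*Protocol article*

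**What the plan says.** The Outcomes section of the protocol article lists "medication uptake from T1 to T2" as the last of four secondary outcome measures. The footnote to Table 2 gives the time points: "T1; at the end of the counselling session; T2; at 6 months follow-up". The Secondary outcomes section applies a Mann-Whitney U-test to the same T1-to-T2 window, with three ordered categories: increase, unchanged, decrease.

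Table 2 adds that changes in statins, antihypertensive drugs and glucose-lowering agents "are documented using medical records (T1) and by verifying patients’ pill-packages (T2").

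On the timing of the intervention, the section on the intervention group says: "Patients are asked to read and work through the DA, at least one week before the group counselling session". It also says: "A physician is to be consulted if patients wish a change of treatment regimens". Controls receive a stress-management brochure over the same lead time.

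The Data collection section lists among the baseline characteristics "current medication, and previous participation in diabetes patient education programmes". The sources for baseline and outcome data are the clinic's electronic patient record and standardised forms.

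**The concern.** A change score should start from a value that the intervention cannot have touched. Here the stated starting point falls after both parts of the ISDM programme. If a patient reads the decision aid, has a drug started, stopped or its dose changed, and the record shows this by the end of the session, the new regimen is the reference. The T2 reading then agrees with it and the patient counts as unchanged.

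Programme-prompted changes arise only in the ISDM arm, so this loss is one-sided. At stake is a diluted comparison on one secondary outcome. Knowledge and treatment goals have to be recorded after the session; medication does not, and an earlier medication record is already planned.

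**Working it through.** **Order of events in the ISDM arm**

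1. Baseline characteristics, including current medication (Data collection). The collection date is not stated.
2. Decision aid read at least one week before the session; no upper limit is given. According to the Background section, it covers benefits and harms of the options and includes a risk assessment tool.
3. Group counselling: joint risk assessment, outcome probabilities, goal setting.
4. End of the session = T1. Medication is taken from medical records. The date of the entry is not stated.
5. Six months = T2. Medication is checked from pill packages.

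**Conditions for a lost change.** All three must hold:

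- the change was prompted by the programme;
- it was made between steps 2 and 4;
- it was in the record read for T1.

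If the third fails, the T1 value is in effect the baseline value and the change is counted at T2. Early change is possible: the Setting section says that the educators adapt insulin dosages, and patients are under regular care in the same clinic.

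**The plan's own figure.** The article gives no figure for this outcome. Its sample size for knowledge (difference 0.2, SD 0.4, two-sided 5%, power 80%) reproduces. The normal approximation gives 2 × (1.96 + 0.84)² × 0.4² / 0.2² = 62.7, so 63 per group. The exact t-test gives 63.8, so 64 per group, with power 80.1%. I use 64 per arm below; nothing else in the point depends on it.

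**Illustration of size.** Every rate here is assumed: an increase in 10% of controls and, truly, 30% of ISDM patients; a decrease in 5% of each arm. Let f be the share of programme-driven increases already in the T1 record. Then

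- observed ISDM increase = 10% + 20% × (1 − f)
- observed difference = 20 × (1 − f) points

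Power is for the planned Mann-Whitney test, from 3,000 simulated trials per row.

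| f | Observed ISDM increase | Observed difference | Power |
|---|---|---|---|
| 0 | 30% | 20 points | about 70% |
| 0.05 | 29% | 19 points | about 65% |
| 0.10 | 28% | 18 points | about 62% |
| 0.25 | 25% | 15 points | about 49% |
| 0.50 | 20% | 10 points | about 27% |

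The documents allow f = 0, and the course of care described makes the low rows the likelier ones.

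**Patients who never attend.** Analyses are by intention to treat, and about 15% non-response or drop-out is expected (Sample size). That rate is not split by cause. A randomised patient who attends no session has no T1 as defined, whereas a baseline record exists regardless of attendance.

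**The case against.** The strongest reply is that the T1 value comes from medical records, not from a check with the patient at the session. Baseline medication may come from the same electronic record. With neither entry dated, the two readings could be identical, and then nothing is lost. This stands, and it is why the loss is only possible. It does not rescue the wording: if the reference is really the pre-intervention entry, T1 is the wrong name for it.

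The described pathway also puts most changes after T1. Risk is assessed jointly and goals are set during the session, and a physician is consulted if the patient then wishes a change. Those changes are counted. This stands too, and it argues for a small f.

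An early change is not invisible elsewhere. Statin use, blood pressure and HbA1c at T2 enter the goal-achievement outcomes. So the damage is confined to the medication-change item.

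Finally, T1 is when goals are recorded, which gives the T1-to-T2 window some logic. That is a reason to keep the T1 record as a description, but not to make it the reference for a between-arm comparison.

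A reader might infer that switches between drugs are lost because of T1. The document does not support this: the three-level scale has no category for a switch from any starting point.

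**Conclusion.** The point holds as a conditional one. By the article's own definitions, medication change is counted from a time after exposure to the programme, although an earlier reference is planned. A programme-prompted change made and recorded before T1 can therefore be coded as unchanged, in the ISDM arm only.

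The size is unknown, probably small, and zero if the T1 record predates the intervention. The table shows how a loss would act; it is not an estimate. Dilution towards no difference assumes that the changes lost go in the same direction as the programme's overall effect. Reading *baseline* as pre-intervention is reasonable, but the article does not date it.

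A reader might infer that early changes are in fact being lost, or that the comparison is seriously biased. The document supports neither, because it gives no date for the T1 entry and no rate of change before the session.

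Severity is minor: this is the last-listed secondary outcome, neither primary nor key secondary.

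**What to change.** In the Outcomes section, the Secondary outcomes section and Table 2, define medication change as running from baseline to T2 in both arms. Take the baseline value from the current medication already listed under Data collection, using the record entry dated before the decision aid or the brochure is handed out. Keep the T1 record as descriptive.

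The cost is small: the wording in three places, and fixing the date of the baseline entry. No new variable is needed, and patients who miss the session gain a defined reference value.

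The change does not cure a separate problem. The reference still comes from medical records and T2 from pill packages, and that difference alone can create apparent changes in both arms.

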### Data collection

The EPRS of the clinic and standardised forms are used to collect baseline characteristics and outcome measures.

Baseline characteristics include age, gender, first-language, social status [31], smoking status, blood pressure, LDL-cholesterol, total cholesterol, HbA1c, current medication, and previous participation in diabetes patient education programmes.

Baseline risks of myocardial infarction are calculated by using a risk assessment tool based on age, smoking status, and clinical parameters. The tool is derived from the Framingham function and calibrated [32] to the average heart attack risk in the German population.

Knowledge is assessed directly after the counselling session and at 6 months follow-up. The individual treatment goals regarding smoking cessation, glucose control, blood pressure control, and statin treatment are assessed after the counselling session. Achievement of treatment goals is assessed during a consultation at 6 months follow-up. Current medication is monitored by verifying patients’ pill-packages. Smoking status is assessed by using a standardised interview question. Current blood pressure values (mean of 2 weeks) are extracted from patient diaries. If values are not available, blood pressure is measured before counselling by a nurse applying a standardised procedure (after 5 minutes seated position). Glucose control is assessed by measuring HbA1c-levels [33].

### Data synthesis

All statistical analyses are carried out according to the intention-to-treat principle. Missing data will be imputed using the method of multiple imputation if feasible. All analyses will be computed using IBM SPSS Statistics 19.0 for Windows.

Baseline characteristics are described using means of standard deviation (± SD) or frequencies, as appropriate according to the level of measurement.

#### Primary outcome

Unpaired t-tests will be used to compare mean scores of knowledge and realistic expectations directly after counselling.

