### Randomisation and blinding

Randomisation is performed in blocks of 8 to ensure close balance of numbers of participants in each group and sufficient numbers of participants (n = 4) in each counselling session. Randomisation sequence is generated independently by the Centre for Clinical Studies at the Jena University Hospital.

Patients are blinded to study group allocation. Allocation is concealed during data entry and analysis.

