### Sample size

We hypothesise patients in the ISDM group to reach higher levels of knowledge and realistic expectations. Based on pilot studies conducted during the development phase of the knowledge test, we estimate that participants having received the intervention will reach 70% correct answers in the knowledge test, whereas those having received the control-intervention will reach 50% correct answers. We calculate the sample size providing 80% power to detect an absolute difference of 20% between the intervention and the control group, using a two-tailed t-test at the 5% level of significance. Estimating a standard deviation (SD) of 0.4 in both groups, data on about 64 patients per group (128 participants) need to be included in data-analysis. Estimating a non-responder/drop-out rate of about 15%, 154 participants will need to be recruited for randomisation.

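### Knowledge is tested straight after counselling in groups of four, but the primary t-test and the sample size treat patients as independent; any within-session correlation makes the test anti-conservative

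*Protocol article*

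**What the plan says.** Under Randomisation and blinding, the block size of 8 is chosen partly to secure "sufficient numbers of participants (n = 4) in each counselling session". Table 1 (Study interventions) gives a group size of 4 for both arms. Data collection places the first knowledge test (T1) directly after the session.

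The primary analysis is an individual-level comparison: "Unpaired t-tests will be used to compare mean scores of knowledge and realistic expectations directly after counselling". The Secondary outcomes section names further unpaired t-tests, Fisher's exact tests and a Mann-Whitney test, also on individuals.

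The Sample size section derives its figure "using a two-tailed t-test at the 5% level of significance". Its target is "80% power to detect an absolute difference of 20% between the intervention and the control group". It concludes that "data on about 64 patients per group (128 participants) need to be included in data-analysis".

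No section mentions an ICC, a design effect, a session or educator term, or a robust standard error. The only cluster design mentioned is a separate future trial in primary care (Discussion).

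**The concern.** Patients in one session share an educator, a discussion and a test situation just before the primary outcome is measured. Table 3 says that, where understanding is poor, the educator corrects answers and repeats information at the end of the session, so content adapts to the group. Scores within a session may therefore be positively correlated.

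The unpaired t-test assumes that they are not. If they are, its standard error is too small, its confidence interval too narrow and its p-value too low. The sample size rests on the same assumption.

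This is not a detail left to an unseen analysis plan. The protocol itself names the tests and the sample-size method, and both assume independence.

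**Working it through.** **Inputs from the protocol.** Means of 0.70 ("participants having received the intervention will reach 70% correct answers in the knowledge test") and 0.50 ("those having received the control-intervention will reach 50% correct answers"), so a difference of 0.20. SD 0.4 ("Estimating a standard deviation (SD) of 0.4 in both groups"). Two-sided 5% level, 64 analysed per arm, session size m = 4.

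**Assumption.** The ICC is not given. I use 0.01 to 0.20.

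**Step 1: reproduce the plan's figure.** The standardised effect is 0.20/0.4 = 0.5. The t-test solution for 80% power is 63.8, so 64 per arm, with power 80.1%. The figure reproduces under independence, with almost no slack.

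**Step 2: formulas.**
- Design effect: DE = 1 + (m − 1) × ICC = 1 + 3 × ICC.
- True standard error divided by the one used: √DE.
- True type I error of the planned test: 2 × [1 − Φ(1.96/√DE)].
- Power of a valid analysis: t-test power at an effective n of 64/DE per arm.
- Rejection rate of the planned test under the alternative: Φ[(0.5/√(2/64) − 1.96)/√DE], where 0.5/√(2/64) = 2.83.

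Example at ICC 0.10: DE = 1.30 and √DE = 1.14. Then 1.96/1.14 = 1.72, giving a type I error of 8.6%. The effective n is 64/1.30 = 49.2 per arm, giving power of 69%.

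**Step 3: same ICC in both arms.**

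| ICC | DE | Type I error, planned t-test | Rejection rate, planned t-test | Power, valid analysis | Power, session-mean t-test (30 df) |
|---|---|---|---|---|---|
| 0.01 | 1.03 | 5.4% | 80% | 79% | 77% |
| 0.02 | 1.06 | 5.7% | 80% | 78% | 76% |
| 0.05 | 1.15 | 6.8% | 79% | 74% | 72% |
| 0.10 | 1.30 | 8.6% | 78% | 69% | 67% |
| 0.20 | 1.60 | 12.1% | 75% | 60% | 58% |

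The 30 degrees of freedom come from 64/4 = 16 sessions per arm: 2 × 16 − 2. A simulation of 16 sessions of 4 per arm (20,000 replicates) gave type I errors of 6.5%, 8.7% and 12.4% for the planned test at ICC 0.05, 0.10 and 0.20. The session-mean test stayed at about 5%.

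**Step 4: clustering in the intervention arm only.** The average inflation is [(1 + 3 × ICC) + 1]/2.

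| ICC (intervention arm) | Average DE | Type I error, planned t-test | Power, valid analysis |
|---|---|---|---|
| 0.05 | 1.075 | 5.9% | 77% |
| 0.10 | 1.15 | 6.8% | 74% |
| 0.20 | 1.30 | 8.6% | 69% |

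**Step 5: smaller sessions.** If 15% loss leaves 4 × 0.85 = 3.4 patients per session on average, DE is 1 + 2.4 × ICC. That is 1.12 at ICC 0.05 and 1.24 at 0.10, with type I error of 6.4% and 7.8%.

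**The case against.** Several counter-arguments carry weight.

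- **The ICC is unknown.** Patients are randomised individually at one clinic, so correlation can arise only after allocation. At 0.01 to 0.02 the effect is small. A reader might infer that type I error does exceed 5%; the protocol does not support that as fact, only as a consequence of a positive ICC.
- **The control sessions do not teach the tested content.** They cover nutrition, sports and stress coping, so an equal ICC in both arms may overstate the harm. Step 4 shows that the excess over 5% is then roughly halved, though not removed.
- **Delivery is standardised.** Table 3 describes common curricula and media, trained educators and video feedback. This argues against the upper end of the range, but it is not a statistical adjustment.
- **The two harms do not fall on one test.** A reader might infer that the planned t-test has both an inflated type I error and 60% to 74% power. It does not: it still rejects in about 79%, 78% and 75% of trials at ICC 0.05, 0.10 and 0.20, because its standard error is too small. The lower power belongs to a valid analysis.
- **An SD of 0.4 is conservative.** A score between 0 and 1 can have an SD of at most √(0.5 × 0.5) = 0.50 at mean 0.50 and √(0.7 × 0.3) = 0.46 at mean 0.70. With SD 0.3 (an assumption), power would be about 94%, 91% and 85% at ICC 0.05, 0.10 and 0.20 in both arms. That answers the power point but not the standard errors.
- **Six-month goal achievement is different.** It is judged at a later consultation against individual goals, without the shared test situation. A reader might extend the same harm to it, but nothing in the protocol supports a comparable ICC there.

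What remains is that the stated primary test is anti-conservative under any positive session correlation, and the protocol makes no allowance for one.

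**Conclusion.** The point holds in conditional form. The protocol fixes a group-delivered intervention with an immediate outcome, and also fixes an analysis and sample size that assume independence. Over an assumed ICC of 0.01 to 0.20, the planned primary test runs at about 5.4% to 12.1% if both arms cluster equally. It runs at about 5.9% to 8.6% for ICC 0.05 to 0.20 if only the intervention arm clusters. The effect is minor at 0.01 to 0.02 and becomes material from about 0.05.

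The stated 80% power at a true 5% level is met only under independence, on the plan's own SD. The conclusion is firmest for T1 knowledge. It is plausible but unquantified for knowledge at six months, and weak for goal achievement.

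**What to change.** 1. Record a session identifier for every patient.
2. Make the primary T1 knowledge comparison a linear mixed model with arm as a fixed effect and session as a random effect. Let the session variance differ by arm, and use small-sample degrees of freedom.
3. State how randomised patients who attended no session enter the model, either as clusters of one or under their assigned session, so that the intention-to-treat principle in Data synthesis is kept.
4. Apply the same session adjustment to knowledge at six months and to the sufficient-knowledge proportions. For six-month goal achievement, use it as a sensitivity analysis.
5. In Sample size, restate power over an ICC range such as 0.01 to 0.20, without enrolling more patients.

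The cost is one extra variable and revised analysis wording. Confidence intervals become slightly wider (by a factor of √1.15 = 1.07 at ICC 0.05, before the degrees-of-freedom correction), and the stated power falls somewhat. If the ICC proves near zero, little is lost: the session-mean test still has about 78% power.

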#### Sub-group analyses

Two groups of participants will be defined regarding their level of knowledge (sufficient / insufficient). Fisher’s exact tests will be used to assess if knowledge is associated with the level of numeracy (yes/no) and with achievement of goals (yes/no). T-test for paired samples will be used to assess differences in knowledge between T1 and T2 in the intervention group. Analyses of variance (ANOVA) will be used to assess if knowledge is associated with age (groups 40–49; 50–59; 60–69). Spearman’s Rho correlation coefficient will be used to assess if knowledge is associated with social status.

Mann Whitney U-tests will be calculated to assess if heart attack risk and social status are associated with the achievement of goals (yes/no).

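### The primary knowledge comparison is a valid but unadjusted t-test; prespecified adjustment for age and social status, both already collected, would probably give a modest gain in precision at almost no cost

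*Protocol article*

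**What the plan says.** The Primary outcome section of the protocol article fixes the method: "Unpaired t-tests will be used to compare mean scores of knowledge and realistic expectations directly after counselling". Neither the secondary nor the sub-group analyses contain a covariate-adjusted comparison of knowledge between the arms.

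The Data collection section says: "Baseline characteristics include age, gender, first-language, social status", followed by clinical measures. Knowledge itself is measured only at T1 (end of the session) and T2 (6 months), so no baseline score exists. Table 2 places numeracy at T1 as well.

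The Objectives section lists the relation between social status and knowledge as an additional question. Under Sub-group analyses, Spearman's coefficient "will be used to assess if knowledge is associated with social status", and an ANOVA does the same for three age groups.

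The Randomisation and blinding section describes blocks of 8, intended to balance group numbers and fill the sessions. It states no stratification factor.

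The Sample size section is built on the unadjusted test: "We calculate the sample size providing 80% power to detect an absolute difference of 20% between the intervention and the control group". The method it names for this is a two-sided t-test at 5%.

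**The concern.** Where a baseline variable predicts the outcome, including it in the model removes part of the between-patient variance and accounts for any chance difference between the arms in that variable. Here the variables are in hand before the outcome is measured, cannot be altered by the counselling, and interest the investigators enough to be analysed against knowledge separately. They are left out of the one comparison where they could sharpen the treatment estimate.

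Nothing else that the article describes does this job: there is no pre-counselling knowledge score, and no stratification by age or social status is stated. On its own assumptions the trial has 80.1% power, so it has no margin. If the arms turn out to differ in age or social status, an adjustment chosen after seeing the data would also be open to dispute, which one fixed in advance would not be.

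**Working it through.** **Inputs from the Sample size section**

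- Intervention: "participants having received the intervention will reach 70% correct answers in the knowledge test". Control: "those having received the control-intervention will reach 50% correct answers". Difference 0.70 − 0.50 = 0.20.
- "Estimating a standard deviation (SD) of 0.4 in both groups", so the standardised difference is 0.20/0.4 = 0.5.
- Two-sided 5% level, 64 evaluable per group, about 15% loss, 154 to be randomised.

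**Step 1: reproduce the plan's figure.** The noncentral t calculation for a standardised difference of 0.5 and 80% power gives 63.8, hence 64 per group, as stated. Power at 64 per group is 80.1%. Inflating for loss, 128/0.85 = 150.6, so 151; the stated 154 is close to this and slightly generous. The sample size is consistent with the unadjusted t-test.

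**Step 2: effect of adjustment.** Let R² be the share of within-arm variance in the T1 score explained by the covariates. The document gives no value, so R² is an assumption shown over a range.

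- Residual SD = 0.4 × √(1 − R²)
- Power from the noncentral t with standardised difference 0.5/√(1 − R²), 64 per group
- 95% CI half-width = 1.979 × residual SD × √(2/64)
- Equivalent unadjusted group size = 64/(1 − R²)

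| R² (assumed) | Power | CI half-width | Equivalent n per group |
|---|---|---|---|
| 0 | 80.1% | 0.140 | 64 |
| 0.02 | 80.9% | 0.139 | 65 |
| 0.05 | 82.1% | 0.136 | 67 |
| 0.10 | 84.1% | 0.133 | 71 |
| 0.20 | 88.1% | 0.125 | 80 |

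The interval narrows by 1 − √(1 − R²): 1 − √0.95 = 2.5% at R² = 0.05 and 1 − √0.80 = 10.6% at R² = 0.20. This proportion does not depend on the SD.

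**Step 3: cost of the extra parameters.** A rough allowance for k added parameters multiplies the noncentrality by √(1 − k/126) and uses 126 − k degrees of freedom.

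| R² (assumed) | Power, k = 2 | Power, k = 3 |
|---|---|---|
| 0 | 79.5% | 79.2% |
| 0.05 | 81.5% | 81.2% |
| 0.10 | 83.5% | 83.2% |
| 0.20 | 87.5% | 87.3% |

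The cost is about 0.5 to 1 point. Setting √(1 − k/126) equal to √(1 − R²) puts break-even near R² = 2/126 = 1.6% for two parameters and 3/126 = 2.4% for three.

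**Step 4: chance imbalance.** For one covariate with correlation ρ to the score, random imbalance moves the unadjusted estimate with an SD of ρ × 0.4 × √(2/64) = ρ × 0.0707. That is 1.4 percentage points at ρ = 0.2, 2.1 at 0.3 and 2.8 at 0.4 (ρ assumed), against a target difference of 20 points.

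**The case against.** The strongest case on the other side is that nothing here is wrong. Randomisation keeps the unadjusted t-test unbiased with its nominal type I error as far as covariates are concerned, and the trial was sized for exactly that test. This stands. A reader might infer that the primary analysis is invalid or biased for lack of adjustment; the document does not support that.

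A reader might also infer that the plan expects age and social status to predict knowledge. It does not say so: both are posed as open questions, with no direction or correlation given. First language is never linked to knowledge at all, which is why it is only an optional covariate.

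The size of the gain cannot be read from the document. The usual strong covariate, baseline knowledge, does not exist, and numeracy is measured too late to use, so a small R² is realistic; adjustment then gains nothing and costs a little. This also stands.

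It is tempting to say that a chance imbalance would carry over in full to the primary difference. It would be scaled by the covariate's correlation with the score, and across repeated randomisations that variation is already in the t-test's standard error.

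Finally, an SD of 0.4 is large for a proportion score. If the SD were 0.3 or 0.2 (assumption), unadjusted power would already be about 96% or over 99%, and power would not be the weak point. The proportional narrowing of the interval would remain.

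Possible correlation within counselling sessions of four affects the t-test and the linear model alike. It is a separate matter and does not decide this one.

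**Conclusion.** The point holds as a modest efficiency improvement. The article fixes an unadjusted primary comparison while recording two plausible, pre-intervention covariates that it intends to study against knowledge anyway. Using them would very likely give equal or better precision, and would settle in advance how an imbalance in age or social status is handled.

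Under an assumed R² of 0.05 to 0.20, power goes from 80.1% to about 82% to 88% before the parameter allowance, or about 81% to 87.5% after it. Below an R² of roughly 2% there is no net gain, and at zero the loss is under 1 point. These figures also take the plan's difference of 0.20, SD of 0.4 and 64 per group as given, and treat patients as independent. The absence of stratification is what the article shows; a fuller protocol might say more.

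**What to change.** Replace the primary analysis sentence with a prespecified linear model: T1 knowledge score on arm, age (continuous) and social status, with first language as an optional further term. Fix the coding of social status in advance. Report the adjusted mean difference with its 95% CI as the primary result, and keep the unpaired t-test as a supportive analysis. State that numeracy is not a covariate, because it is measured at T1, after the counselling.

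The change should be dated and made before allocation is revealed to the analyst. It costs one or two sentences. It needs no new data and no additional patients, the sample size can stay as it is, and the model runs in the software already named. Missing covariate values fall under the multiple imputation already planned.
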